**Methods:**

This single blinded randomized control trial will include 120 women with a BMI of 25–45 kg/m^2^, ≥21 years of age, and undergoing in vitro fertilization (IVF) treatments. Participants will be randomized to standard of care (*N* = 60) or an intervention group (*N* = 60) in a block design by polycystic ovary syndrome status. The intervention will combine a dietary component (Mediterranean meal plan) with exercise prescription following the Physical Activity Guidelines for Americans. Participants will be assessed pre- and post-intervention. The standard of care group will be offered to join the intervention group if the IVF treatments are unsuccessful as a cross over design. Recruitment is anticipated to start in July of 2021. Primary outcomes will include single oocyte gene expression profiles and follicular fluid metabolites. Mann-Whitney U nonparametric tests will be used to assess potential differences for each stratum. Follicular fluid and serum metabolites will be analyzed using a one-factor Analysis of Covariance (ANCOVA) at four levels, pair-wise comparisons using Tukey-Kramer post-hoc tests will be used to identify groups whose means differ significantly while retaining the family-wise error rate at 5%. When the design is balanced, two-way Analysis of Variance (ANOVA), or non-parametric Friedman test will be used in data analysis. Additionally, general linear models and ANCOVA may be used to control for covariates. Significance will be set at *p* < 0.05. Findings will be disseminated via peer-reviewed manuscripts and presentations at scientific conferences.

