##### Oocyte, cumulus cell, and follicular fluid data collection

AF&GA will provide the research team with oocytes (eggs), cumulus cells (cells surrounding the egg), and follicular fluid (liquid surrounding the egg that also contains granulosa cells) that are not needed for the IVF procedures (e.g., too many eggs retrieved). These samples will be collected during the standard oocyte retrieval procedures performed as part of standard care for the participants undergoing fertility treatment. Participants will undergo standard procedures at AF&GA for ovarian stimulation, which include hormonal superovulation and oocyte retrieval 36 h after human gonadotropin injection. Any deviations from the standard clinic procedures will be documented and sensitivity analyses will be performed to determine whether deviations to stimulation protocol yielded in significant differences. It is possible that the research team will not obtain samples in the case that the retrieval yields only enough eggs for the IVF procedures. In this case, only follicular fluid will be obtained. The research team will not obtain samples that could have been fertilized or frozen as agreed with the participant prior to the retrieval procedure. The research team will obtain only samples that are unneeded by the clinic. Thus, no additional treatment or clinical procedures will be required for the participants. The embryologist at the clinic will collect the cumulus cells during the processing of the oocytes. Granulosa cells will be isolated from the follicular fluid by centrifugation at 4000 rpm for 10 min. Follicular fluid samples contaminated with blood will not be used for analysis. Samples will be placed on ice and transported by the research team to the ACNC where they will be stored in messenger RNA lysis buffer and frozen at − 70 °C until processing. Oocytes and cumulus cells will be used to study gene expression while follicular fluid will be used to measure metabolites and hormones that may be influenced by diet and exercise. Both mRNA and genomic DNA will be isolated from individual oocytes as previously described [9]. cDNA libraries will be prepared and fragmented cDNA will be evaluated to determine size distribution of the libraries. Samples will be sequenced using the NextSeq 500 System (Illumina). Individual libraries will be generated and RNA-Seq will be conducted. Sequencing reads from each sample will be trimmed and filtered before being aligned to the human genome (hg19). All data will be analyzed using SeqMonk and R software. Differentially expressed gene expression will be identified using the DESeq2 package which will include multiple testing corrections. Serum and follicular fluid glucose, total cholesterol, and triglyceride levels will be assessed using colorimetric or electrochemiluminescence assays. Serum and follicular fluid insulin, leptin, tumor necrosis factor (TNF)-α, C-reactive protein (CRP), and interleukin-6 will be measured using enzyme-linked immunosorbent or electrochemiluminescence assay kits. Serum lipid profiles—non-esterified fatty acids, high-density lipoprotein, and low-density lipoprotein— will be analyzed by enzymatic methods on a clinical analyzer. All assays will be performed in accordance with the manufacturers’ instructions.

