#### Statistical analyses

Prior to inferential analyses, exploratory data methods will be used to check for potential outliers and aberrant observations and measurements. The following will be tested between the PCOS and no PCOS groups to assess potential differences: fertility diagnosis (male factor, ovulatory disorder, tubal factor, endometriosis or unexplained), pregnancy, live birth, age and race using Mann-Whitney U nonparametric tests for each strata. Follicular fluid and serum metabolites will be analyzed using a one factor Analysis of Covariance (ANCOVA) at four levels because of the potential unbalanced data structure. Pair-wise comparisons using Tukey-Kramer post-hoc tests will be used to identify groups whose means differ significantly while retaining the family-wise error rate at 5%. If the distributional assumptions for ANOVA are not met, and if a suitable data transformation is not found, a Kruskal-Wallis equality-of-populations rank test will be used, followed by Dunn’s test of multiple comparisons. When the design is balanced, two-way ANOVA or non-parametric Friedman test will be used in data analysis. As alternatives, generalized linear models may be also used to test the effects of treatment and presence of PCOS and ANCOVA may also be used to control for additional confounding factors Correlations will be determined using the Pearson Product Moment or the Spearman Rank Order for non-parametric tests. Significance will be set at *p* < 0.05. RNA-seq data will be analyzed using SeqMonk and R software. Gene expression levels will be expressed as raw read counts for differential expression analysis and as log-transformed normalized reads per kilobase per million mapped reads for visualization. Differentially expressed gene expression will be identified using the DESeq2 package and filtered at ± two-fold change and statistical significance with a *p* value ≤0.05. Gene Ontology (GO), transcription factor (TF) target analysis, and pathway analyses will be conducted with DAVID bioinformatics and/or WebGestalt, which include multiple testing corrections. For participants assigned to the standard of care whose fertility treatments were unsuccessful, they will be offered to re-enroll and be directly assigned to the intervention group. The data from these participants will be analyzed separately, using paired t-tests or non-parametric equivalent to evaluate the effect of the intervention (pre and post).

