#### Sample size

Based upon existing data in the literature, a power of 0.8, and a *p*-value set at 0.05, with 20 women per group, we will be able to detect a mean difference of at least 0.37 standard deviation units in follicular levels of C-reactive protein and of insulin. In our previous study, we found follicular fluid CRP differences of 3.2 μg/ml (2.7 vs. 5.9 μg/ml, respectively) between normal weight and obese women [12]. Thus, we are confident that this sample size will be sufficient to detect clinically meaningful differences. Based on our experience, we expect that we will be unsuccessful in obtaining a good quality oocyte from approximately 33% of women enrolled. Therefore, we will enroll 30 women in each of the 4 groups (PCOS- standard of care, PCOS-intervention, no PCOS- standard of care, no PCOS-intervention) to assure that we will have at least 20 oocytes per group.

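### The p ≤ 0.05 threshold for calling genes, a primary outcome, is not identified as an adjusted p value and does not match the multiple-testing correction promised elsewhere in the protocol

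*Protocol article*

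**What the plan says.** The abstract's Methods paragraph sets the status of the outcome: "Primary outcomes will include single oocyte gene expression profiles and follicular fluid metabolites".

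Two sections then describe how differentially expressed genes are found.

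- Oocyte, cumulus cell, and follicular fluid data collection: "Differentially expressed gene expression will be identified using the DESeq2 package which will include multiple testing corrections". Neither the method of correction nor an error level is named.
- Statistical analyses: the DESeq2 step is "DESeq2 package and filtered at ± two-fold change and statistical significance with a *p* value ≤0.05". The words adjusted, padj, q value and false discovery rate do not appear. The following sentence attaches correction to the enrichment tools: "pathway analyses will be conducted with DAVID bioinformatics and/or WebGestalt, which include multiple testing corrections". The section's general rule is also a plain one: "Significance will be set at *p* < 0.05".

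No section calls the p value for gene calling raw, nominal or unadjusted. In the statistical section the word raw describes only the read counts.

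**The concern.** The sentence with the numbers in it is the one an analyst will code. DESeq2 returns a p value and, separately, an adjusted p value. Someone working from the statistical section as written would filter on the first; someone working from the data collection section would filter on the second. The two choices give different gene lists for a primary outcome, and the protocol does not say which list is the result.

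The literal choice controls neither the family-wise error rate nor the false discovery rate. The two-fold filter may remove many false calls or few, depending on how variable expression is between oocytes, so it guarantees no error rate. A claim that the intervention changed the oocyte transcriptome could then rest on a list that is not empty when nothing has changed. The gene ontology, transcription factor and pathway analyses would start from that list, and correcting the enrichment p values does not remove false genes from it.

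**Working it through.** **The two statements side by side.** The data collection section promises correction at the gene level but gives no cut-off. The statistical section gives the cut-off but no correction at the gene level, and names correction one step later. The same section states family-wise control at 5% for the metabolite comparisons (Tukey-Kramer), so error control is spelled out there but not for gene calling.

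**Inputs from the protocol.**
- Evaluable oocytes: 20 in each of four arms (Sample size). The stated enrolment reproduces: 20 / (1 − 0.33) = 29.9, so 30 per arm.
- Pooling the two PCOS strata gives about 40 v 40 for intervention against standard of care.
- Threshold 0.05 (taken as two-sided) and two-fold change, i.e. |log2 fold change| ≥ 1.

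**Inputs assumed, because the protocol gives none.** 10,000 to 15,000 genes tested; mean count 50; negative-binomial dispersion 0.25 to 2; no gene truly different.

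**p value alone.** Expected null genes called = G × 0.05: 10,000 × 0.05 = 500 and 15,000 × 0.05 = 750.

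**p value plus two-fold filter.** For one gene, approximately:
- SD(log2) = √(1/50 + dispersion) / ln 2
- SE = SD × √(2/n), with n oocytes per side
- the gene passes if |log2 fold change| exceeds the larger of 1 and 1.96 × SE; under the null this has probability P = 2 × [1 − Φ(max(1/SE, 1.96))]

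Example, dispersion 1, n = 20: SD = √1.02 / 0.693 = 1.457; SE = 1.457 × √0.1 = 0.461; 1/SE = 2.17; P = 0.030; 10,000 × 0.030 = 300 and 15,000 × 0.030 = 450.

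| Dispersion | SD(log2) | P, 20 v 20 | Null genes called | P, 40 v 40 | Null genes called |
|---|---|---|---|---|---|
| 0.25 | 0.75 | 0.00002 | fewer than 1 | about 0 | about 0 |
| 0.5 | 1.04 | 0.0024 | 24–36 | 0.00002 | fewer than 1 |
| 1 | 1.46 | 0.030 | 300–450 | 0.002 | 21–32 |
| 2 | 2.05 | 0.050 | 500–750 | 0.029 | 290–440 |

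**Check by another method.** A simulation using t-tests on log2 values gave the same pattern. At 20 v 20 the share of null genes passing both filters was 0.17%, 3.2% and 4.9% for log2 SD 1.0, 1.5 and 2.0. At 40 v 40 it was about 0%, 0.3% and 2.5%.

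**Effect of adjusting.** Simulated illustration with assumed inputs: 15,000 genes, 300 truly changed by 1.5 on the log2 scale, 20 v 20. Each entry gives false calls out of all calls, averaged over runs.

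| log2 SD | Unadjusted p plus filter | BH-adjusted p plus filter |
|---|---|---|
| 1.0 | 22 of 305 (7%) | 9 of 266 (3%) |
| 1.5 | 467 of 719 (65%) | 3 of 68 (about 5%) |
| 2.0 | 730 of 922 (79%) | 0.3 of 5 (about 3%) |

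**The case against.** The best defence is that nothing here is actually uncorrected. The data collection section says genes will be "identified using the DESeq2 package which will include multiple testing corrections". The statistical section opens its sentence in nearly the same way and adds the cut-offs. Read together, they describe a corrected DESeq2 analysis cut at 0.05, and mentioning correction for the pathway tools does not withdraw it from DESeq2. The name of the correction and its level are details an article may leave to the full protocol or analysis plan.

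Much of this stands. A reader might infer that the protocol specifies a raw p value and so contradicts itself outright; the text does not support that, because the word unadjusted would have to be supplied by the reader. What does not stand is the idea that nothing needs changing. The article prints a numeric threshold for a primary outcome, and as printed it can be followed in a way that departs from the other section.

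Three objections on size are also fair.

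- Gene count, dispersion and mean count are assumptions, and the result runs from almost none to several hundred. The protocol does not say where this trial lies.
- The contrast between intervention and standard of care with strata pooled is about 40 v 40, where the counts at dispersion 0.5 and 1 fall more than ten-fold. A reader might also multiply the counts by the number of contrasts among the four arms, but the protocol names no RNA-seq contrasts.
- Null genes scattered at random would not systematically favour any one pathway, and the enrichment tests are themselves corrected. Co-expression weakens that protection by an amount not quantified here.

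**Conclusion.** The point holds as a mismatch between two sections about the rule for a primary outcome. The statistical section does not identify its 0.05 as an adjusted value; the data collection section promises correction. Taken literally, the statistical section controls no error rate.

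If the unadjusted value were used, the consequence would range from negligible to several hundred null genes: at 20 v 20, fewer than 1 at dispersion 0.25 and up to 500–750 at dispersion 2; at 40 v 40, about 0 up to 290–440. These figures rest on the assumed gene count, mean count and dispersion, on no true effect, and on a normal approximation. If the authors already intend the adjusted value, none of this arises and only the wording is at fault.

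This is therefore a clarification to make before the sequencing data are analysed, not a demonstrated error in the analysis and not a reason to hold up the trial.

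**What to change.** In Statistical analyses, replace the plain p value in the gene-calling rule with: Benjamini-Hochberg adjusted p value (DESeq2 padj) ≤ 0.05 and at least a two-fold change. This brings the section into line with the data collection section. State that the gene ontology, transcription factor and pathway tools take that list, or the full ranked list, as input.

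The change is one line of text, and DESeq2 already outputs the value. The cost is a shorter gene list, possibly much shorter if expression is highly variable: in the illustration above, from 719 to 68 genes at log2 SD 1.5, with most of the genes removed being false calls, though some true ones are lost too (from about 252 to about 65, that is 719 − 467 and 68 − 3).

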#### Standard of care

Participants in the standard of care group will be provided with dietary and physical activity recommendations from the Dietary Guidelines for Americans at their first study visit and will follow the standard of care practice at AF&GA up to their retrieval procedures. Participants will not be required to wait 8 weeks prior to their retrieval procedures since no intervention is needed. If participants in the standard of care group plan to undergo a second oocyte retrieval cycle, they will be offered to join the intervention group at that time as a cross over design.

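### The extension of standard-of-care women into the intervention is called a crossover and tested with paired tests as the intervention effect, but it has one fixed order and no control

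*Protocol article*

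**What the plan says.** Three places in the protocol article describe what happens to standard-of-care women after their first cycle.

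- **Abstract, Methods:** the standard-of-care group "will be offered to join the intervention group if the IVF treatments are unsuccessful as a cross over design".
- **Standard of care:** the condition is different. "If participants in the standard of care group plan to undergo a second oocyte retrieval cycle", then "they will be offered to join the intervention group at that time as a cross over design".
- **Statistical analyses:** the group is "participants assigned to the standard of care whose fertility treatments were unsuccessful", and "they will be offered to re-enroll and be directly assigned to the intervention group". On the analysis: "The data from these participants will be analyzed separately", "using paired t-tests or non-parametric equivalent to evaluate the effect of the intervention (pre and post".

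The analysis is not labelled exploratory or descriptive. No adjustment for cycle number, elapsed time or selection is stated for it. The general significance level of 0.05 is set in the same section without exempting it.

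**The concern.** A crossover trial estimates a treatment effect within person because participants are randomised to different orders, so that period effects can be separated from treatment. Here there is one order only. The paired test will detect any systematic change between the two measurements, whatever its cause, and the protocol says in advance that this change is the effect of the intervention. Entry also depends on how the first cycle turned out, so the women are not a random subset of the standard-of-care group.

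What is at stake is the meaning of a significant paired result. As the text stands, it could be read as within-woman evidence of efficacy when the intervention had done nothing.

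**Working it through.** The protocol gives no sample size, power or expected change for this subset, so there is no stated figure to reproduce. The structural argument needs no numbers; the sizes below rest on assumptions.

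**1. Structure.** Let the mean paired difference be D = T + P + S, where T is the intervention effect, P the effect of order and time, and S the shift due to selection. Estimating T needs either women in the reverse order or women having a concurrent second cycle on standard of care. The protocol provides neither, so T cannot be separated from P and S, however many women enrol.

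**2. What pre and post can mean.** The text allows two readings, and the outcome decides between them.

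- *Oocytes and follicular fluid.* Table 1 and the section on oocyte, cumulus cell and follicular fluid collection place these at retrieval only. The pair must be first retrieval against second, so P is the full effect of a second stimulation plus elapsed time. The periods also differ by design: the Standard of care section waives the 8-week wait before retrieval, while the intervention is expected to last 8 to 12 weeks.
- *Serum, fitness and anthropometrics.* Table 1 places these at visits 1 and 3, so the pair may be the two visits after re-enrolment. P is then not a first-versus-second-cycle effect. But visit 3 falls within 5 days of a retrieval that follows hormonal superovulation, so the interval takes in ovarian stimulation, again without a concurrent control.

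**3. Regression to the mean (first against second retrieval).** Assumed inputs: 60% of first cycles fail; correlation of the first marker value with failure liability, ρ = 0.2 to 0.4; within-woman correlation between cycles, r = 0.3 to 0.7.

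- Mean liability among the 60% selected: φ(0.253)/0.60 = 0.386/0.60 = 0.644.
- If failure relates to the second value only through the first, the expected shift is 0.644 × ρ × (1 − r).
- Smallest: 0.644 × 0.2 × 0.3 = 0.039 SD. Largest: 0.644 × 0.4 × 0.7 = 0.180 SD.
- If failure instead reflects only a stable marker level, it is equally related to both cycles and the expected shift is 0.

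The range is therefore 0 to about 0.18 SD. The direction is towards improvement only for a marker adversely related to failure.

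**4. Effect on the paired test when T = 0.** Simulation of a two-sided paired t-test at 0.05: 60 standard-of-care women, 50% or 70% failing and all re-enrolling, r = 0.3 to 0.7, 3000 runs per scenario. Selection acts through the first value only.

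| Scenario | False-positive rate |
|---|---|
| No selection, no order shift | 0.046 to 0.051 |
| Selection only, ρ = 0.3 | 0.064 to 0.116 |
| Order shift only, 0.2 SD | 0.138 to 0.368 |
| Order shift only, 0.4 SD | 0.445 to 0.905 |
| ρ = 0.3 and order shift 0.2 SD | 0.376 to 0.513 |

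The order shifts are illustrative; the protocol gives no value. The scenarios describe retrieval-to-retrieval pairs and do not carry over directly to visit 1 against visit 3 after re-enrolment, because selection acted on the earlier cycle.

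**5. Entry rule.** The Abstract and Statistical analyses require unsuccessful treatment; Standard of care requires a planned second retrieval. A woman can meet both, but neither condition implies the other, and only a second retrieval yields the second oocyte or follicular-fluid value.

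**The case against.** The strongest reply is that this is a side analysis. The trial is randomised, the metabolite analysis is a four-level ANCOVA, gene expression goes through DESeq2, and nothing says that the paired result feeds the primary conclusion. The crossover label is loose, but the text states plainly what is done: an offer, re-enrolment and direct assignment. Labelling an analysis exploratory and choosing how to report it are often left to the statistical analysis plan, which is not shown.

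Much of this stands, and it limits the point. It does not remove it, because the purpose of the paired test is stated in the protocol itself, and that purpose cannot be met by this design. The entry wordings also overlap largely, so that inconsistency is minor.

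A reader might infer more than the document supports:

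- *That second-cycle samples, pregnancies or births leak into the randomised comparison.* The Statistical analyses section keeps these women's data separate. It tests pregnancy and live birth between PCOS and non-PCOS groups and states no treatment-arm comparison of them that such data could enter.
- *That regression to the mean must produce a shift.* It need not; the lower bound is zero.
- *That every outcome carries the full effect of cycle order.* That reading is forced only for oocytes and follicular fluid.

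**Conclusion.** The stated purpose of the paired analysis is wrong as written, and the crossover label is a misnomer. For oocyte and follicular-fluid outcomes, treatment is completely confounded with cycle order and time. For measures at visits 1 and 3 after re-enrolment, the result is an uncontrolled change that spans stimulation. Neither conclusion depends on an assumed number.

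The size of the resulting bias is unknown. Regression to the mean contributes 0 to about 0.18 SD under the assumptions above. The order effect could be larger or smaller, and the document gives nothing from which to estimate it.

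The point concerns a separately analysed, non-randomised subset. It does not invalidate the randomised comparison. It is worth correcting because the text gives an uncontrolled change a causal reading.

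**What to change.** In Statistical analyses, replace the purpose given in "using paired t-tests or non-parametric equivalent to evaluate the effect of the intervention (pre and post" with a statement that the extension yields an uncontrolled, exploratory within-woman change, reported with a 95% CI; that this change does not estimate the intervention effect; and that the efficacy conclusion rests on the randomised comparison only. State there which two measurements form the pair for each type of outcome.

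Remove the crossover label from the Abstract and from Standard of care, and call this an uncontrolled extension. Reconcile the entry wording between the Abstract and Statistical analyses on one side and Standard of care on the other.

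These are wording changes, with no new data or visits. The price is a weaker claim from the extension.
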